### Sample size

The sample size calculation was made using the G*Power software (version 3.1) [33]. A priori analysis was performed with the following input parameters: effect size (0.25) [7], type I error (0.05), type II error (0.95), number of groups (3), number of measurements (3), and a correlation between group (0.5). Also, the loss rate of 20% was considered. Thus, our analysis revealed a sample size of 66 subjects, divided into three groups of 22 participants.

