**Methods:**

This protocol is a randomized controlled clinical trial with a sample of 66 older adults divided into three groups: supervised exercise (SUP = 22), home-based exercise (HB = 22), and supervised plus home-based exercise (SUP+HB = 22). The multicomponent exercise program will last 12 weeks, three times per week, for 60 min per session and include warm-up, balance, muscle-strengthening, gait, and flexibility exercises. The study’s primary outcomes will be neuromuscular function, composed of the assessment of muscle isokinetic strength, muscle architecture, and neuromuscular electrical activation. The secondary outcome will be physical function, usual and maximum gait speed with and without dual-task, and quality of life. All outcomes will be assessed at baseline and post-intervention (week 12).

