### Statistical methods

For data analysis, the results will be reported using descriptive statistics and mean and standard deviation. All data will be analyzed by intention-to-treat, with baseline scores substituted for missing follow-up data. The Shapiro-Wilk test will be applied to verify the normality of the data and the Levene test for the sample’s homogeneity. For parametric data, a comparison between groups and periods (pre and post-training) will be analyzed by an ANOVA of mixed-models with Bonferroni’s post-hoc test. When differences between groups were observed at the baseline, a covariance analysis (ANCOVA) will be applied. In addition, a Pearson’s correlation coefficient (r) was calculated to verify the magnitude of the possible observed effects, considering r = .10 as a small effect, r = .30 as a medium effect, and r = .50 as a large effect [34]. P-values less than 0.05 will be considered statistically significant. The tests will be performed using the IBM SPSS Statistics software version 25.

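### The sample size is computed for three measurement occasions but the trial has two; 66 enrolled with 20% loss do not give 0.95 power for the two-occasion design (about 0.90 at the plan's own inputs)

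*Protocol article*

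**What the plan says.** The Sample size section lists the G*Power inputs as an effect size of 0.25, alpha of 0.05, and then "type II error (0.95), number of groups (3), number of measurements (3), and a correlation between group (0.5"). It then adds: "Also, the loss rate of 20% was considered". The result is 66 participants, 22 per group.

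The rest of the article describes two occasions. The Abstract (Methods) says: "All outcomes will be assessed at baseline and post-intervention (week 12"). Trial design places the assessments before randomization and again after three months. Statistical methods plans a mixed-model ANOVA for "a comparison between groups and periods (pre and post-training"). The two laboratory days described under Measurements both belong to the baseline evaluation, so they do not supply a third occasion.

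Statistical methods also plans an intention-to-treat analysis in which a missing follow-up value is replaced by that participant's baseline score.

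**The concern.** For a group-by-time interaction with a given f, the noncentrality parameter in G*Power rises in proportion to the number of measurements. Entering three where the trial has two therefore makes a given number of participants look more informative than it is. The sample size section is the only justification for 66, and it describes a design that the rest of the article does not.

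Two labels in the same sentence add to the difficulty. Read literally, "type II error (0.95") means 5% power. The 0.5 is called a correlation between groups, but parallel randomized groups are independent; the input that G*Power takes here is the correlation among repeated measures. Neither label changes the total, but nobody can reproduce the calculation as printed.

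At stake is whether the stated power and the stated loss allowance can both be true for the trial being run.

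**Working it through.** **Inputs.** From the Sample size section: f = 0.25, alpha = 0.05, k = 3 groups, m = 3 measurements, 20% loss, total 66. The 0.95 is read as power (1 − beta) and the 0.5 as rho, the correlation among repeated measures. From the Abstract, Trial design and Statistical methods: m = 2 in the actual trial.

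**Formula.** Repeated-measures ANOVA, within-between interaction, sphericity assumed:

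- lambda = f² × N × m / (1 − rho)
- df1 = (k − 1)(m − 1), df2 = (N − k)(m − 1)
- power = probability that a noncentral F(df1, df2, lambda) exceeds the 5% critical value of the central F.

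**Step 1: reproduce 66 with the stated m = 3.**

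- N = 51: lambda = 0.0625 × 51 × 3 / 0.5 = 19.125, df 4 and 96, power 0.946.
- N = 52: lambda = 19.5, df 4 and 98, power 0.950. This is the smallest N that reaches 0.95.
- N = 54 (equal groups): lambda = 20.25, df 4 and 102, power 0.958.

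Allowing for loss: 52 / 0.8 = 65; 54 × 1.2 = 64.8; 54 / 0.8 = 67.5. The first two become 66 when rounded up to three equal groups. So 66 is reachable from the stated inputs, although the article does not say which inflation was used. The other repeated-measures options do not fit at m = 3: the within-subject main effect needs 43 to 45 before loss, and the between-group main effect needs 168.

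**Step 2: look for another origin of 66.** With m = 2 and no loss added:

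- N = 65: lambda = 0.0625 × 65 × 2 / 0.5 = 16.25, df 2 and 62, power 0.950.
- N = 66 (equal groups): lambda = 16.5, df 2 and 63, power 0.953.

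So 66 is also exactly the two-occasion total in equal groups, before any loss.

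**Step 3: power of the two-occasion design after 20% loss.** 66 × 0.8 = 52.8, about 53 completers.

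| Completers | lambda | df | Power |
|---|---|---|---|
| 52 | 13.00 | 2, 49 | 0.889 |
| 53 | 13.25 | 2, 50 | 0.896 |
| 54 | 13.50 | 2, 51 | 0.902 |

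The type II error among completers is then about 10%, against the 5% implied by 0.95 power. For scale, holding 0.95 after 20% loss would take 65 / 0.8 = 81.25 to 66 / 0.8 = 82.5, that is 82 or 83 enrolled, or 84 in equal groups.

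**Step 4: sensitivity to rho (53 completers, m = 2).**

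| rho | lambda | Power |
|---|---|---|
| 0.3 | 9.46 | 0.77 |
| 0.5 | 13.25 | 0.90 |
| 0.7 | 22.08 | 0.99 |

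**Step 5: the planned handling of missing data.** Substituting baseline scores keeps all 66 in the analysis but sets the change of each lost participant to zero. As a rough assumption, let f shrink by the loss rate: 0.25 × 0.8 = 0.20. Then lambda = 0.04 × 66 × 2 / 0.5 = 10.56, df 2 and 63, power 0.82.

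**The case against.** The strongest reply is that little is lost. Completer power of about 0.90 is above the commonly used 0.80, no endpoint or analysis changes, and the two labelling slips do not affect the total. That stands, and it is why this is a point that should be fixed and not one that puts the trial in doubt.

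Three stronger readings are tempting, and the article does not support them.

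- **That 66 proves the calculation was run with three occasions.** A reader might infer this because the stated inputs lead to 66. But two occasions with no loss added also give 66, with fewer rounding choices. The 3 may be a real input error, or it may be a misprint with the loss allowance never applied. The article does not settle which. After loss the result is the same.
- **That 0.90 is the power of the planned analysis.** It is the power of a completer analysis at rho = 0.5. The plan analyses everyone with baseline scores substituted, so the true figure may be lower; the 0.82 above shows the direction but rests on a crude dilution assumption. The rho of 0.5 is given without a source, and the spread from 0.77 to 0.99 is wider than the gap between 0.95 and 0.90.
- **That adjusting for baseline would restore the power.** ANCOVA multiplies lambda by 2 / (1 + rho) = 1.33, so for 53 completers lambda = 13.25 × 1.33 = 17.67 and power is 0.96. That holds only for 53 completers, rho = 0.5 and no baseline substitution. Under the rough dilution above, with 66 analysed, it is about 0.92 (lambda = 10.56 × 1.33 = 14.08). The article also plans ANCOVA only when groups differ at baseline.

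**Conclusion.** The point holds. The number of measurements in the Sample size section contradicts the design stated elsewhere in the article, and the stated 0.95 power, the 20% loss allowance and the total of 66 cannot all hold for two occasions. This does not depend on how 66 was obtained.

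The size is moderate: about 0.90 in place of 0.95 after loss. That figure rests on the interaction test, the article's own f, alpha and rho (with 0.5 read as the correlation among repeated measures), and about 53 completers with no dilution. Power of 0.95 is reached only if all 66 complete. This should be fixed as a matter of correct reporting; the documents do not show that the trial is too small.

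**What to change.** In the Sample size section:

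- Enter two measurements.
- Label 0.95 as power (1 − beta), not type II error.
- Label 0.5 as the correlation among repeated measures.
- State that the test sized is the group-by-time interaction, if that is so, and how the 20% loss was applied.
- Report that 66 enrolled give about 0.90 power after 20% loss (about 53 completers, correlation 0.5, no dilution), and 0.95 only with no loss. A line giving the range over plausible correlations, and noting that baseline substitution may lower power, would make the figure honest.

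If a gain from baseline adjustment is cited, state the conditions under which it holds.

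The cost is one corrected paragraph, plus the registry entry if it carries the figure. No increase in enrolment is requested. The only downside is a slightly less favourable stated power.

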### Adverse outcomes

Aiming to prevent the sample from performing exercises wrongly, and in order to avoid falls and fractures, the exercise will be monitored by physical education professionals as well as physiotherapists. Nevertheless, the participants will be monitored by the Rating of perceived Exertion to ensure the recommended intensity level, avoiding the deleterious effect of high-intensity exercise in older populations. In the case of muscle injury, physical training will be suspended.

### Statistical methods

For data analysis, the results will be reported using descriptive statistics and mean and standard deviation. All data will be analyzed by intention-to-treat, with baseline scores substituted for missing follow-up data. The Shapiro-Wilk test will be applied to verify the normality of the data and the Levene test for the sample’s homogeneity. For parametric data, a comparison between groups and periods (pre and post-training) will be analyzed by an ANOVA of mixed-models with Bonferroni’s post-hoc test. When differences between groups were observed at the baseline, a covariance analysis (ANCOVA) will be applied. In addition, a Pearson’s correlation coefficient (r) was calculated to verify the magnitude of the possible observed effects, considering r = .10 as a small effect, r = .30 as a medium effect, and r = .50 as a large effect [34]. P-values less than 0.05 will be considered statistically significant. The tests will be performed using the IBM SPSS Statistics software version 25.

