## Materials and methods

### Trial design

It is a protocol for a randomized controlled clinical trial, investigator-blinded, with three parallel groups. Participants are individually randomized to one of the three groups in a 1:1:1 allocation ratio. The Research Ethics Committee approved the project at the Federal University of Paraná, Brazil (UFPR) (CAAE:20181219.4.0000.0102). The study protocol was developed based on the Standard Protocol Items: Recommendations for Interventional Trials (SPIRIT) guidelines [12]. The study follows the CONSORT guidelines [13], and all the items from the World Health Organization Trial Registration Data Set were registered in the publicly accessible Brazilian Registry of Clinical Trials (RBR-7MZ2KR). Any change made to the protocol will be reported to the Research Ethics Committee and modified in the Brazilian Registry of Clinical Trials.

The enrolled participants’ assessments will be carried out at baseline prior to randomization, and after three months, as described below (Fig 1).

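### Substituting the baseline score for a missing week-12 value scores that participant as zero gain; this shrinks arm contrasts when loss is equal and can create false ones when it is not

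*Protocol article*

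**What the plan says.** The rule is in the Statistical methods section: "All data will be analyzed by intention-to-treat, with baseline scores substituted for missing follow-up data". It covers all outcomes, and the article names no other missing-data method. The abstract's Methods paragraph gives a single follow-up: "All outcomes will be assessed at baseline and post-intervention (week 12". The main analysis is a mixed ANOVA, described as "a comparison between groups and periods (pre and post-training) will be analyzed by an ANOVA of mixed-models with Bonferroni’s post-hoc test". The Sample size section anticipates missing data ("Also, the loss rate of 20% was considered") but gives no rate by arm.

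The Intervention groups section gives all three arms a 12-week exercise programme. The Introduction expects SUP+HB to do better than HB and to give benefits similar to SUP. No similarity margin is stated.

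**The concern.** Intention-to-treat means analysing people in the arm to which they were randomised. It does not require this particular substituted value. With only two time points, baseline substitution fixes the change score at zero, in a trial where every arm is trained and gains are the premise. The substituted values also enter the ANOVA as if they had been measured.

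Two things are at stake. First, supervision is the randomised factor and could affect who returns at week 12 as well as how well people train; the rule would turn a retention difference into an apparent neuromuscular difference. Second, even with equal retention all contrasts are pulled towards zero. That is not safely conservative here, because one of the two hypotheses is that two arms are alike.

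**Working it through.** **Inputs from the protocol.** The Sample size section gives "effect size (0.25) [7], type I error (0.05), type II error (0.95") and "number of groups (3), number of measurements (3), and a correlation between group (0.5"). The 0.95 makes sense only as power. Also stated are 20% loss, 66 participants and 1:1:1 allocation (22 per arm). Gains by arm and loss by arm are not given, so everything that uses them below is an assumption.

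**1. The plan's own figure.** For the group-by-time interaction, λ = f²·N·m/(1 − ρ). With f = 0.25, m = 3, ρ = 0.5, α = 0.05 and power 0.95, N = 54 in equal groups (power 0.958). Then 54 × 1.2 = 64.8, which becomes 66 in three equal arms. The stated 66 is reproduced. The inflation pays for lost observations; it does not pay for a shrunken contrast. (Three measurements were entered where the design has two. That is a separate matter; m = 2 is used below.)

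**2. What the rule does to a mean.** Let d be an arm's proportion without a week-12 value, g_c the mean gain of those observed and g_m the mean gain the others would have shown.
- True all-randomised gain: (1 − d)·g_c + d·g_m
- Gain under the rule: (1 − d)·g_c
- Error in that arm: −d·g_m

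The error is zero only if g_m = 0. If loss is unrelated to outcome (g_m = g_c = g), the arm mean becomes (1 − d)·g.

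**3. Equal 20% loss, unrelated to outcome.** Every contrast is multiplied by 0.80: 0.60 SD becomes 0.48, 0.40 becomes 0.32, and a true SUP versus SUP+HB difference of 0.20 becomes 0.16. In simulation the SD of the SUP–HB estimate (gains 0.5 SD, ρ 0.5) is 0.276, against 0.338 with observed data. That is not real precision: 0.276/0.80 = 0.345 once the shrinkage is undone.

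Power at the planned effect: with m = 2, λ = 0.0625 × 66 × 2/0.5 = 16.5. With one low arm and a change-score SD of 1, 22 × (2/3) × D² = 16.5, so D = 1.06 SD. Simulated power is about 0.89–0.90 with observed data and about 0.81–0.87 under the rule. The lower end applies when the lowest arm itself gains 0.4 SD.

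**4. Unequal loss, equal true gains.** The false contrast is g × (difference in loss). Type I error of the group-by-time test comes from simulation with 22 per arm and loss unrelated to outcome within arm. Repeated runs agree to within about one percentage point.

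| Assumed gain, all arms | Assumed loss SUP/HB/SUP+HB | False SUP–HB contrast | Type I error under the rule |
|---|---|---|---|
| 0.5 SD | 15/25/15% | 0.5 × 0.10 = 0.05 SD | about 5–6% (ρ 0.5) |
| 0.8 SD | 10/30/10% | 0.72 − 0.56 = 0.16 SD | about 8% (ρ 0.5), about 12% (ρ 0.8) |

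Analysing observed data keeps type I error near 5% in these scenarios. The sign follows the arm that loses more: with gains of 0.5 SD, losses of 10% in SUP and 30% in HB give +0.10 SD, and the reverse gives −0.10 SD.

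**The case against.** The strongest reply is that zero gain may be close to the truth for people lost because they stopped exercising, and that comparisons with observed data favour observed data because they assume loss unrelated to outcome. This has force. Suppose those observed gain 0.8 SD, those missing would have gained 0.2 SD, and loss is 10% in SUP and 30% in HB. The true all-randomised gap is (0.72 + 0.02) − (0.56 + 0.06) = 0.12 SD. Baseline substitution gives 0.16 (error 0.04); observed data give 0.00 (error 0.12). If those missing gain nothing, substitution is exactly right. So the rule deserves a place as a sensitivity analysis. It does not follow that it should be the only analysis, since the protocol offers no argument that missing participants gain nothing.

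Three stronger readings are tempting, and the documents do not support them.
- A reader might infer that everyone who drops out of training is scored as zero gain. The rule touches only missing follow-up values. Someone who stops training but attends week 12 keeps the measured value, and nothing in the article says such people go unassessed.
- A reader might infer that the rule works in favour of the hypothesis that HB does worse. The direction is unknown. The Introduction presents home programmes as suited to people with limited mobility or time, and the Discussion notes that supervised participants must travel, so SUP could lose more. The distortions can also cancel: true gains of 0.6 and 0.2 SD with 10% and 30% loss give 0.54 − 0.14 = 0.40, the true contrast.
- A reader might take 12% as the expected type I error. It needs a 0.8 SD gain, a threefold loss difference and ρ = 0.8, none of which is in the protocol.

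**Conclusion.** The concern holds, conditionally. The rule is a stated choice for all outcomes, not a detail left to another document, and the algebra is certain: each arm's mean gain is understated by its loss proportion times the gain its missing participants would have had. At the protocol's own 20% loss, if equal across arms and unrelated to outcome, contrasts shrink to 80% of their true value; with equal gains, type I error stays near 5%, so the harm is dilution. With unequal loss a false contrast appears in either direction, from about 0.05 SD with negligible inflation to 0.16 SD with type I error of about 8–12%, all on assumed gains and loss by arm. Confidence is high in the mechanism and limited in its size and sign. This is a should-fix.

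**What to change.** In Statistical methods, replace the substitution rule for the primary analysis with a baseline-adjusted model of week-12 values in all randomised participants, with missing values handled under missing at random by likelihood or multiple imputation. Arm and baseline value belong in the model. Adherence should be an auxiliary variable only if the imputation is stable with 22 per arm. Keep baseline substitution as a named sensitivity analysis for the case where those missing gain little or nothing, and report missing week-12 values by arm so that readers can judge which assumption fits.

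The cost is revised wording and modest analysis work, with no extra participants or visits. The downside is reliance on missing at random, which the data cannot verify, and slightly wider, more honest standard errors.

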#### Physical function

The physical function will be assessed using the Short Physical Performance Battery Test [29] and the Senior Fitness Test [30], aiming to verify muscle strength, agility, and dynamic and static balance. The Short Physical Performance Battery Test is composed of tandem, semi-tandem, side-by-side stands balance test, 4-meters walking speed test, and 5-times sit-to-chairs stand test. The Senior Fitness Test is composed of 5 times sit to chair stand test, arm curl test (number within 30 seconds), chair sit and reach test (distance between fingers and toe), back scratch test (distance between the two third fingers), Timed-up-and-go (time to rise, walk 3 m and return to the chair) and 6-minute walk test (distance walked in 6 minutes).

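### The only stated comparison of arms over time is reserved for outcomes that pass a normality test on the trial's own data, so the analysis can differ between outcomes by chance

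*Protocol article*

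**What the plan says.** The rule is in the Statistical methods section of the protocol article. It begins with "The Shapiro-Wilk test will be applied to verify the normality of the data" and adds Levene's test for homogeneity. The comparison of arms follows: "For parametric data, a comparison between groups and periods (pre and post-training) will be analyzed by an ANOVA of mixed-models with Bonferroni’s post-hoc test". No comparison is named for outcomes that are not judged parametric.

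A second switch that depends on the data comes next: "When differences between groups were observed at the baseline, a covariance analysis (ANCOVA) will be applied". The section ends with "P-values less than 0.05 will be considered statistically significant", without saying whether that level also applies to the preliminary tests.

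The Sample size section fixes the numbers per arm: "our analysis revealed a sample size of 66 subjects, divided into three groups of 22 participants". The abstract gives two assessments, baseline and week 12, so each outcome has six group-by-period cells.

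**The concern.** The trial asks whether gains differ between the three modalities, which is the group-by-period contrast. Under the stated rule, an outcome reaches that contrast only after a non-significant normality test. The same question may then be answered by different methods for different outcomes, depending partly on sampling noise.

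The gate also protects against little. The model needs roughly normal errors, and with equal arms of 22 the F test tolerates moderate departures from them. A significance test of normality does not measure whether a departure matters for the comparison of arms.

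At stake are how comparable the results are across a long list of primary and secondary outcomes and, depending on the unstated fallback, power for outcomes that fail.

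**Working it through.** **The plan's own figures.** The article gives no failure rate for the normality test, so there is none to reproduce. Its sample size, which supplies the 22 per arm, does reproduce. For the repeated-measures interaction with f = 0.25, three groups, three measurements and correlation 0.5, the noncentrality at N = 54 is 0.25² × 54 × 3 / (1 − 0.5) = 20.25. Power is then 0.958. With 20% added, 54 × 1.2 = 64.8, or 66 in equal groups.

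**Inputs for the check.** Three arms of 22 and two periods (article). Level 0.05 for Shapiro-Wilk (assumed). Pre-post correlation 0.5 (the Sample size section's correlation input, read as the correlation between repeated measures) and 0.8 (assumed).

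**Step 1: truly normal outcomes that fail.** For k independent tests at 0.05, the chance of at least one rejection is 1 − 0.95^k. Levene's test is not counted.

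| What is tested | k | 1 − 0.95^k | Simulated, 22 per arm |
|---|---|---|---|
| One pooled residual set | 1 | 5.0% | 5 to 6% |
| Two pooled periods | 2 | 9.8% | 10 to 11% |
| Three sets of change scores | 3 | 14.3% | 14 to 15% |
| Six group-by-period cells | 6 | 26.5% | 25 to 26% |

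**Step 2: bounded scores.** The article gives no means, SDs or ceiling rates for the Short Physical Performance Battery or the SF-36, so every line here is an assumption. With six-cell testing and 22 per arm, the share of outcomes that fail is:
- battery score, mean 10 to 10.5, SD 1.5: 99 to 100%
- battery score, mean 9, SD 2: 81%
- SF-36 scale in 25-point steps, mean 75, SD 35: 100%
- SF-36 scale, mean 75, SD 20: 77%
- SF-36 scale, mean 65, SD 18: 33%

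The same scenarios give 20 to 95% when change scores are tested and 6 to 100% when pooled residuals are tested.

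**Step 3: what a fallback would cost.** Take normal data with one arm 0.5 SD above the other two at week 12. The squared deviations of the arm means sum to 0.5² × 2/3 = 0.167, and the noncentrality is 22 × 0.167 / V. With two periods, the mixed-ANOVA interaction is a one-way ANOVA on change, so V = 2(1 − r). For ANCOVA, V = 1 − r².
- r = 0.5, mixed ANOVA: 3.667 / 1.00 = 3.67, power 0.37
- r = 0.5, ANCOVA: 3.667 / 0.75 = 4.89, power 0.47
- r = 0.8, mixed ANOVA: 3.667 / 0.40 = 9.17, power 0.76
- r = 0.8, ANCOVA: 3.667 / 0.36 = 10.19, power 0.80

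Simulation agrees to within 0.01 (0.38, 0.48, 0.75 and 0.79). The rank tests were simulated:

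| Analysis | r = 0.5 | r = 0.8 |
|---|---|---|
| Kruskal-Wallis, week-12 values only | 0.35 | 0.35 |
| Kruskal-Wallis, change | 0.35 | 0.73 |
| Mixed ANOVA (as stated) | 0.37 to 0.38 | 0.75 to 0.76 |
| ANCOVA for all outcomes | 0.47 to 0.48 | 0.79 to 0.80 |

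**The case against.** The strongest reply is that this is a condensed journal article. What exactly is tested, any transformation and the method for non-normal outcomes commonly sit in a fuller document that is not shown, so the missing fallback is no fault. That stands. It does not remove the point, because naming a fallback would still leave the choice between methods to a test on the trial data.

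A reader might infer three stronger things that the article does not support:
- **About a quarter of normal outcomes fail.** This needs six separate cell tests at 0.05, with one rejection enough to disqualify the outcome. The article specifies none of this, and other usual readings give 5 to 15%.
- **Nearly all bounded scores fail.** This rests on assumed distributions. It fits scores at the ceiling or in coarse steps, but one mid-range SF-36 scenario gave 33%.
- **Failing outcomes lose the group-by-period test.** The article is silent here. A transformation or a rank test on change would still compare gains between arms.

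The reply is also right that the gate's cost must be measured against the mixed ANOVA, which is what a passing outcome would get, and not against ANCOVA. At correlation 0.5, most of the gap between a week-12 rank test and ANCOVA comes from baseline adjustment.

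Finally, it is fair to say that testing within cells is nearly the same as checking residuals. The wording therefore does not prove that raw pooled scores are tested.

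**Conclusion.** The point holds as a weakness in a stated rule: the analysis of each outcome is conditional on a preliminary test of its own data. A truly normal outcome would fail in about 5 to 26% of cases, depending on a unit of testing that the article does not give and on an assumed level of 0.05. Ceiling-bound or coarse scores would fail more often, to an unknown degree.

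The loss of power depends on the unstated fallback. It is 2 to 3 points if ranks of change are used. If baseline is ignored, it is again about 2 to 3 points at correlation 0.5 but about 40 points at 0.8. These figures assume normal data, complete follow-up at 22 per arm and a 0.5 SD difference in one arm.

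The case for change does not rest on a large loss. It rests on having one analysis fixed in advance. Using ANCOVA throughout would also raise power over the stated mixed ANOVA by about 10 points at correlation 0.5 and about 4 points at 0.8.

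**What to change.** Remove the Shapiro-Wilk and Levene tests as conditions for choosing the analysis. For every continuous outcome, pre-specify one comparison of the arms at week 12 adjusted for the baseline value of that outcome (ANCOVA), to be used whatever a normality test shows. This would also replace the rule that applies ANCOVA only after a baseline difference has been seen.

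Check residual plots, and report heteroscedasticity-robust or bootstrap intervals as a sensitivity analysis. An ordinal model for the Short Physical Performance Battery score is a reasonable option but not essential.

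The cost is a revised paragraph in the statistical methods and slightly more analysis work. The baseline values are already collected, so no extra data are needed.

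### ANCOVA is applied only if a baseline difference is observed, so the model for each outcome turns on chance or judgement and the more precise analysis is usually forgone

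*Protocol article*

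**What the plan says.** For parametric data, the Statistical methods section of the protocol article sets the default: "a comparison between groups and periods (pre and post-training) will be analyzed by an ANOVA of mixed-models with Bonferroni’s post-hoc test". The next sentence gives the exception: "When differences between groups were observed at the baseline, a covariance analysis (ANCOVA) will be applied". It does not say what counts as an observed difference, in which variables it is looked for, or which covariate then enters. The general significance rule is "P-values less than 0.05 will be considered statistically significant". Missing week-12 values are replaced by the participant's baseline value under intention to treat.

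Two design facts bear on this. Trial design states 1:1:1 individual randomisation with baseline assessed beforehand. The Abstract states that every outcome is measured at baseline and at week 12 only.

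**The concern.** Baseline precedes randomisation, so a difference between arms at baseline is a chance event. Testing for it answers no question about the treatments, yet here it decides which model estimates the effect. Since the article does not define an observed difference, the choice may also be made by judgement after data are seen.

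What is at stake is mainly precision in a trial of 22 per arm. The baseline is collected on everyone, but its most efficient use is kept for the few outcomes that trip the trigger. Imbalances just short of the trigger are handled only by subtraction, which over-corrects them. Some effects would be reported as adjusted week-12 differences and others as differences in change, so the tables would mix two kinds of estimate. This is a stated decision rule, not a detail left open, and an analysis plan that followed it would inherit the fault.

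**Working it through.** **Inputs.** Sample size section: "effect size (0.25) [7], type I error (0.05), type II error (0.95"), where 0.95 is read as power; "number of groups (3), number of measurements (3), and a correlation between group (0.5"), where 0.5 is read as the correlation among repeated measures; and "the loss rate of 20% was considered".

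**1. The plan's own figure.** For the within-between interaction in a repeated-measures ANOVA, λ = f²·N·m/(1−ρ), with df (k−1)(m−1) and (N−k)(m−1). With f = 0.25, k = 3, m = 3 and ρ = 0.5, N = 54 gives λ = 0.0625 × 54 × 3/0.5 = 20.25 and power 0.958; N = 51 gives 0.946. Adding 20% gives 54 × 1.2 = 64.8, which is 66 when rounded up to three equal groups; 54/0.8 gives 68. The stated 66 is therefore reproduced closely, which supports this reading of 0.5 without proving it.

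**2. What the default test is.** With two occasions, the group-by-time interaction is an ANOVA of week 12 minus baseline. Per unit of σ²:
- change score: 2(1−ρ)
- ANCOVA: 1−ρ²
- ratio, ANCOVA to change: (1+ρ)/2

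| ρ | Change | ANCOVA | Variance saved |
|---|---|---|---|
| 0.5 | 1.00 | 0.75 | 25% |
| 0.7 | 0.60 | 0.51 | 15% |
| 0.8 | 0.40 | 0.36 | 10% |
| 0.9 | 0.20 | 0.19 | 5% |

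At ρ = 0.5 the change-score variance equals that of week-12 values alone. ANCOVA would there be worth 66/0.75 = 88 participants analysed by change.

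**3. Power for the planned effect, two occasions, ρ = 0.5.** With 66 analysed, λ = 0.0625 × 66 × 2/0.5 = 16.5 for change and 16.5/0.75 = 22 for ANCOVA; power is 0.953 and 0.989. With 54, λ is 13.5 and 18; power is 0.902 and 0.966.

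**4. What the conditional rule recovers.** Simulation with 22 per arm, two arms 0.6 SD above the third (an assumed effect), and a trigger of p < 0.05 on the outcome's own baseline (assumed):

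| ρ | Change always | Conditional rule | ANCOVA always |
|---|---|---|---|
| 0.5 | 0.51 | 0.51 | 0.63 |
| 0.7 | 0.74 | 0.74 | 0.80 |
| 0.8 | 0.90 | 0.90 | 0.92 |

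The trigger fires for about 5% of outcomes, so the rule performs almost exactly like change scores.

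**5. Imbalance below the trigger.** Given a chance baseline difference Δ, the expected error in the change estimate is −(1−ρ)Δ, or half of Δ in the opposite direction at ρ = 0.5. In simulated null trials at ρ = 0.5 with baseline p between 0.05 and 0.10, the change analysis rejects 10.7% of the time, against 4.9% for ANCOVA. With baseline p above 0.5 it rejects only 2.7%. These departures average out across trials: the rule's overall type I error is 0.043 to 0.048.

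**6. Effect of substituting baseline values.** If 20% of week-12 values are replaced and there is no effect, the analysed correlation becomes 0.2 × 1 + 0.8 × 0.5 = 0.6. The variance ratio is then (1+0.6)/2 = 0.80, a saving of 20% rather than 25%. In simulation with the 0.6 SD effect, the power gain at ρ = 0.5 falls from about 12 points to about 7; at ρ = 0.8 it is 2 to 3 points.

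**The case against.** The default analysis is valid. In a randomised trial the group-by-time test is unbiased, and it does use the baseline, as a repeated measure. A reader might infer that the two-stage rule inflates false positives; step 5 shows that overall it does not. A reader might also infer that the baseline is simply wasted. That is true only at ρ = 0.5; above it, change scores keep part of the gain, and ANCOVA's advantage is modest at 0.8 or 0.9.

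Nor do the documents support saying that the plan falls short of its power target for this reason. Baseline substitution keeps all 66 in the analysis, and at 66 the default nominally gives 0.953. A power figure for completers alone does not describe the planned analysis.

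Finally, both the 0.5 and the trigger are open to interpretation. The article calls the former a correlation between groups, and it is a planning input, not an estimate for torque, architecture or gait. The exception could refer to participant characteristics rather than each outcome's own baseline.

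All of this stands, and it limits the size and severity of the point. It does not rescue the rule. On any reading, a chance difference selects the model, and the lack of a definition adds discretion.

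**Conclusion.** The concern holds as a loss of efficiency and consistency, not as a threat to validity. ANCOVA for every outcome would cut variance by 25% at ρ = 0.5, 15% at 0.7 and 10% at 0.8, and by somewhat less with baseline substitution. The conditional rule recovers almost none of this. About 5% of outcomes would switch model by chance. The false-positive rate is distorted given the imbalance actually seen but is not materially inflated overall.

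The variance figures are large-sample results and depend on the pre/post correlation; taking 0.5 for it is an assumption. The 5% assumes a p < 0.05 test on each outcome's own baseline, and the simulated powers assume a 0.6 SD effect. This should be fixed, as a nearly free improvement, but the trial's conclusions do not fail without it.

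**What to change.** Delete the sentence that makes ANCOVA conditional on a baseline difference. Pre-specify instead that, for every continuous outcome analysed parametrically, the week-12 value is modelled on arm with that outcome's own baseline as covariate, whatever the baseline comparison shows. Report adjusted pairwise mean differences with 95% confidence intervals, keeping the planned Bonferroni adjustment.

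The cost is one residual degree of freedom per model. Under the Trial design section, the change must also be reported to the ethics committee and entered in the registry. No new data are needed. It should be made before outcome data are examined by arm.
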